## Background

Perinatal depression (PND) refers to the onset of major depression during pregnancy (antenatal depression, AD) and up to 12 months after delivery (postpartum depression, PPD). The estimated prevalence of PND is roughly 12 % [1] with a three-fold increase in incidence of depression during the postpartum period compared to nullipara [2]. Up to 80 % of women in the postpartum period report some kind of depressive symptoms, which range from a mild and transient form of sadness that is frequently termed “baby blues” to full diagnoses of major depression [3]. The Diagnostic and Statistical Manual of Mental Disorders, 4th edition text-revised (DSM-IV-TR) defined a specific subtype of major depressive disorder as post-partum depression (PPD) when the onset of the depressive episode occurs within 4 weeks after delivery [4]. Indeed, the risk of depression in puerperal women remains high through the first postpartum year [5], and in around 50 % of the cases the onset of depression occurs already during pregnancy. Based on this, the above mentioned, wider definition of perinatal depression (PND) has been adopted. The revised fifth edition of DSM (DSM-V) does not recognise this entity as a separate diagnosis, but as a specifier of major depression by using the term of “perinatal-onset or peripartum”, where a woman has to meet the criteria for major depressive episode with an onset in pregnancy or within 4 weeks of delivery [6]. An unrecognized or an untreated PND increases the risk of preterm delivery [7], smoking and substance use, shortening of breastfeeding [8], abusive behaviour toward children, suicide [9], negative effects on the relationship with the partner and cognitive problems in infants [10]. A significantly higher mean mother-infant daily cost was estimated by the British health system for women with PND compared to women without PND [11]. The absence of defined objective markers for PND diagnosis, which is purely based on the clinical interview and therefore examiner-dependent, is a significant limit to unequivocal and early recognition of the disease. Moreover, to date, except for a history of depression or positive familiar psychiatric history, no certain medical risk factors are known to predict PND [12]. With the exception of theoretical abnormalities in hypothalamic-pituitary-adrenal axis activity and possible genetic risk factors that are shared with a variety of psychiatric disorders, the etiopathogenesis of PND is still unknown. Once PND is recognized, no definitely safe pharmacologic treatments are available during pregnancy and breastfeeding [13], and the concurrent lack of preventive therapies exposes the health of women and children to the PND related risks. Placebo-controlled, randomized trials of antidepressant substances in this population are lacking, and the methodological flaws of available studies limit the generalizability of the findings. A large meta-analysis recently concluded that evidence over benefits/harms of available compounds cannot adequately support informed decisions about the treatment of PND [14]. Furthermore, teratogenicity concerns commonly influence women’s acceptance of potentially effective treatments. Therefore, a safe and effective treatment remains an urgent, currently unmet, clinical need.

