#### Secondary aims

To investigate the relationship between specific genetic polymorphisms and the development of depression during pregnancy and the postpartum (substudy Life-ON 1)To investigate the effectiveness of BLT in treating PND (substudy Life-ON 2).To test whether a short term trial by BLT in non-depressed pregnant women can prevent the onset of PND (substudy Life-ON 3)

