• MINI-International Neuropsychiatric Interview (MINI), clinician rated [53] • MINI-International Neuropsychiatric Interview Plus (MINI Plus), clinician rated • Edinburgh Postnatal Depression Scale (EPDS), self-administered (depression > 12) [54] • Visual Analog Scale for depression (VAS), self-administered (ranging between 0 and 10) [55] • Hamilton Depression Rating Scale - 21 items (HDRS-21), clinician-rated (14–18 = moderate depression, 19–22 = severe depression, ≥ 23 = very severe depression) [56] • Montgomery-Asberg Depression Rating Scale (MADRS), clinician-rated (normal 0–6; mild depression 7–19; moderate depression 20–34; severe depression >34) [57] • Temperament and Character Inventory (TCI), self-administered [58] _•_ Interview for Recent Life Events (IRLE), self-administered [59]
Sleep assessment tools
• Pittsburgh Sleep Quality Index (PSQI), self-administered (good sleeper <5; poor sleeper ≥5) [60] • Insomnia Severity Index (ISI), self-administered [normal ≤7; sub threshold insomnia 8–14; clinical insomnia (moderate severity) 15–21; clinical insomnia (severe) 22–28] [61] • Epworth Sleepiness Scale (ESS), self-administered (normal <10; pathological ≥ 10) [62] • RLS interview (5 criteria), clinician rated [63] and the International RLS Study Group Rating Scale (if RLS diagnosed) [64] • Munich Parasomnia Screening (MUPS), self-administered [65] • Morningness-Eveningness Questionnaire (MEQ), self-administered (16–30 “definite evening types”, 31–41 “moderate evening types”, 42–58 “intermediate types”, 59–69 “moderate morning types”, 70–86 “definite morning types”) [66] • One night of home polysomnography (PSG) • Wrist Actigraphy (7-days of consecutive home recording)

Pregnant women, who will have accepted to participate in the main observational Life-ON study, will also be asked to additionally and voluntarily take in part in the Life-ON 1 substudy (genetic investigation). The substudy Life-ON 2 will be proposed to women who develop PND during pregnancy or during the 9 months’ period after delivery. A random population of non-depressed pregnant women will be asked to participate in the preventive BLT trial Life-ON 3 (substudy). A specific dedicated written informed consent is necessary to participate in each of the above mentioned substudy, and woman can withdraw their consent at any time (Fig. 1).

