### Experimental design – Life-ON study

Life-ON is an observational, longitudinal study, which will systematically and prospectively explore sleep and sleep-related parameters during pregnancy and their correlation with the onset of PND. The expected outcome is to identify reliable, potential, early diagnostic markers of PND.

Demographic and gynaecological/obstetrical data will be collected for all women included in the study. Mood, sleep quality and disorders, and other biomarkers will be assessed at regular intervals during the perinatal period, until 12 months postpartum, in all participants (Additional file 1: Table S1a).

Sleep investigations will include an interview with a sleep expert to determine lifetime and current sleep disturbances, supplemented with questionnaires assessing sleep quality, insomnia, daytime sleepiness, circadian chronotype, sleep-related movement disorders and parasomnias. Unattended ambulatory polysomnography (PSG) will be conducted in all participants between the 23th and 25th gestational week. This will include electroencephalogram (F3, C3,O1 referenced to the contralateral mastoid, M2), bilateral electro-oculogram, surface electromyogram of submentalis muscle and bilateral tibialis anterior muscles, electrocardiogram and sleep respiratory parameters (nasal air flow, thoracic and abdominal respiratory effort, oxygen saturation).

Sleep will be scored by a sleep specialist according to the international guidelines [52]. The rest/activity cycles during pregnancy and postpartum will be assessed by 7-days actigraphic recordings repeated for 3 times: between the 23th and 25th gestational week, around the 3rd (between 90 and 105 days) and between the 11th and the 12th month after delivery.

All participants will undergo a psychiatric and psychological evaluation, including semi-structured interviews and questionnaires for screening depression, stressful life events and selected personality traits. Depressive symptoms will be assessed at the time of study inclusion and approximately every 3 months until the 12th month postpartum with a higher sampling rate (every two weeks) during the two postpartum months; the diagnosis of PND will be always established using structured clinical interviews conducted by staff psychologists/psychiatrists.

### Experimental design – substudy Life-ON 1

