Life-ON 1 substudy consists in a genetic test on a blood sample taken during the 23rd-25th gestational week, with the aim to identify possible specific genetic polymorphisms, that may be associated with PND. Part of the blood samples taken at inclusion will be processed and stored in a bio-bank for future use.

### Experimental design – substudy Life-ON 2

Life-ON 2 is a longitudinal and interventional trial, which will investigate the effectiveness of BLT in treating PND. Women with minor or major depression, diagnosed by a psychiatric interview or with an EPDS score >12 at any time from study inclusion to 9 months postpartum, will be invited to participate in the randomized-controlled BLT trial. Participants will be randomised on a 1:1 basis to receive 6 weeks of morning BLT or dim light placebo. The trial will be single blind. Subjects will be asked to maintain their habitual bedtime and wake-up schedule, and to begin the light treatment within 20 min of habitual wake-up time. Subjects will be instructed to sit in front of the light box (Philips Energy Up HF 3419) at a specified distance (around 30 cm) and to receive an active light dose (10’000 lux) or placebo dim light (50 lux) for ½ hour. Safety will be monitored with the self-report version of the Systematic Assessment of Treatment Emergent Effects (SAFTEE). Similarly to Life-ON, all participants will be followed up until 12 months postpartum.

### Experimental design – substudy Life-ON 3

Life-ON 3 is a longitudinal and interventional trial, in non-depressed women, which will investigate the effectiveness of BLT during pregnancy in preventing PND. A subsample of 80 subjects without depression will be randomly, consecutively recruited to receive 6-week open-label BLT during the third trimester of pregnancy. The selected participants will receive ½ hour of morning BLT (10’000 lux, Philips Energy Up HF 3419) for 6 weeks. Subjects will be asked to maintain their habitual bedtime and wake-up schedule, and BLT is planned to commence within 20 min of habitual wake-up time. Safety will be monitored with the Systematic Assessment of Treatment Emergent Effects (SAFTEE). All participants will be followed-up until 12 months postpartum and the main outcome will be the incidence of postpartum depression in subjects receiving BLT compared to subjects with no treatment.

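### Life-ON 3 aims to prevent perinatal depression, but its main outcome covers postpartum depression only, so the trial as planned cannot support a claim about PND

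*Protocol article*

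**What the plan says.** All references are to the protocol article.

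- **Aim.** Secondary aims says that Life-ON 3 tests whether a "short term trial by BLT in non-depressed pregnant women can prevent the onset of PND". The Life-ON 3 design section repeats that the substudy "will investigate the effectiveness of BLT during pregnancy in preventing PND".
- **Definition.** Background defines PND as "onset of major depression during pregnancy (antenatal depression, AD) and up to 12 months after delivery (postpartum depression, PPD". Antenatal onset is therefore part of PND, and postpartum depression is the part that begins after delivery.
- **Main outcome.** The Life-ON 3 design section states: "the main outcome will be the incidence of postpartum depression in subjects receiving BLT compared to subjects with no treatment".
- **Treatment window.** Women are "recruited to receive 6-week open-label BLT during the third trimester of pregnancy".
- **Sample size and analysis.** Determination of sample size takes its Life-ON 3 incidence from a 12-month postpartum period. Statistical analyses plans a logistic regression on prevention of postpartum depression. It describes one group by the light it received and the other as untreated.
- **Mood checks.** Depressive symptoms are assessed "approximately every 3 months until the 12th month postpartum with a higher sampling rate (every two weeks) during the two postpartum months".
- **Route out of Life-ON 3.** Description of the study says: "The substudy Life-ON 2 will be proposed to women who develop PND during pregnancy" or in the 9 months after delivery. The Life-ON 2 design section says that women found depressed "at any time from study inclusion to 9 months postpartum, will be invited to participate in the randomized-controlled BLT trial", with 1:1 allocation to active or dim light.

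**The concern.** The aim and the main outcome name different conditions, and the difference falls on the weeks in which the intervention is given. Women are free of depression when allocated, so the natural starting point for a prevention question is allocation. By the article's own definitions, the outcome starts at birth.

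Three things follow if pre-birth onsets are not counted:

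- If light prevents onsets only while it is given, the main outcome does not show it.
- If light only delays onset past birth, the main outcome shows more depression with light although total onset is the same.
- A result in favour of light says nothing about antenatal onset, yet the stated aim invites a conclusion about PND as a whole.

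Two features make the boundary at birth less clean. Mood is checked roughly every 3 months before birth but every two weeks just after it, so an antenatal onset may first be seen postpartum. A woman in the no-treatment arm who becomes depressed before birth may also enter Life-ON 2 and receive the same active light. She then no longer fits a group described as untreated.

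**Working it through.** **1. The plan's own figures.** Determination of sample size gives 43 vs 172 women (20 % vs 5 %) and 79 vs 314 (15 % vs 5 %), one-sided alpha 0.05, power at least 80 %. Exact power of the one-sided Fisher test at these sizes is 0.803 and 0.804. The normal approximation with pooled null variance gives 0.839 and 0.831. The figures stand for the postpartum outcome they were set for, and the mismatch does not make them wrong. (Both pairs are close to 1:4, not the stated 1:3; that is a separate matter.) Recruitment is planned at 1:3 until 80 women have had light, so 80 vs 240 is used below.

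**2. Share of onsets before birth.** Assumptions, not in the document: light starts at 28 to 34 weeks, birth is at 40 weeks (w = 12 to 6 weeks before birth), the onset rate is constant to 52 weeks postpartum, and control incidence from allocation is 15 to 20 %. Allocation at the start of light is inferred from the third-trimester treatment window.

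Share s = w/(w + 52):
- w = 6: 6/58 = 0.103
- w = 12: 12/64 = 0.188

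Controls with onset before birth = 240 × rate × s:
- 15 %: 3.7 (w = 6) to 6.8 (w = 12)
- 20 %: 5.0 to 9.0

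Background puts about 50 % of onsets in pregnancy. That covers the whole of pregnancy, so it does not give the share for these weeks.

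**3. Shift in the arm difference if pre-birth onsets are not counted.**
- Light works only during its 6 weeks: shift = rate × 6/(w + 52). At 15 %: 1.55 (w = 6) and 1.41 (w = 12) points. At 20 %: 2.07 and 1.88 points.
- Extreme case, every pre-birth onset delayed past birth: shift = rate × s. At 15 %: 1.55 and 2.81 points. At 20 %: 2.07 and 3.75 points. Example at 20 % and w = 12: 16/80 = 20 % with light, 39/240 = 16.3 % in controls.

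The planned difference is 10 to 15 points.

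**4. Crossover through Life-ON 2.** If every control depressed before birth entered, half would be assigned active light: 3.7 to 9.0 × 0.5 = 1.9 to 4.5 women. Applying the 25 % attrition given for Life-ON 2, × 0.75 = 1.4 to 3.4.

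**5. Power if onset from allocation became the main outcome.** Here 15 % or 20 % vs 5 % is taken as the postpartum part, and the control total is that rate/(1 − s). 80 vs 240, one-sided 0.05, pooled normal approximation:

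| Scenario | w = 6 | w = 12 |
|---|---|---|
| Postpartum only, 15 % vs 5 % | 0.81 | 0.81 |
| From allocation, same relative effect before birth | 16.7 % vs 5.6 %: 0.86 | 18.5 % vs 6.2 %: 0.90 |
| From allocation, no effect before birth | 16.7 % vs 6.7 %: 0.76 | 18.5 % vs 8.5 %: 0.71 |
| Postpartum only, 20 % vs 5 % | 0.98 | 0.98 |
| From allocation, no effect before birth | 22.3 % vs 7.3 %: 0.96 | 24.6 % vs 9.6 %: 0.93 |

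**6. Would the wider outcome detect an effect confined to treatment?** With total onset lower by only 1.4 to 2.1 points, its power is about 0.09 to 0.10.

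**The case against.** The strongest reply is that the operative plan is consistent. The main outcome, the incidence basis and the regression all say postpartum, the sample-size section describes the substudy as prevention of postpartum depression, and PND is the project's umbrella term. On that view the defect is loose wording in two aim sentences. This largely stands, and it is why the remedy is to narrow the aim. It does not remove the point, because the aim sentences determine what the trial will be said to have shown.

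Three stronger readings are tempting, and the document does not support them.

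- **That the main outcome must be replaced.** A postpartum outcome is defensible. It keeps the open-label treatment weeks, when reporting may differ between arms, out of the count, and it uses the densest assessments. With checks about every 13 weeks, the 6 to 12 weeks before birth hold on average only 6/13 = 0.5 to 12/13 = 0.9 scheduled checks. At 15 % vs 5 %, power could fall below the 80 % target.
- **That antenatal onsets are certainly discarded.** No counting rule is stated, and an episode persisting after birth might be recorded as postpartum. Such a rule commonly sits in the full protocol or analysis plan, so its absence from an article is no fault.
- **That the result would be seriously biased.** The shifts are small and would rarely change the test result. The wider outcome would hardly ever detect an effect confined to treatment either. Crossover involves a handful of 240 controls at most.

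**Conclusion.** The point holds as a mismatch between the stated aim and what is measured. Life-ON 3 as planned can support a conclusion about postpartum depression but not about PND, because antenatal onset after allocation belongs to the aim and not to the outcome.

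That conclusion rests on the text alone. The size rests on the assumed 6 to 12 weeks before birth, the constant onset rate and a control incidence of 15 to 20 %. The true pre-birth share could be lower or higher. Under those assumptions about 4 to 9 of 240 controls are affected, and the shift is modest beside the planned difference. The point is worth correcting because the correction is nearly free and changes what may be concluded. It does not invalidate the design or the sample size.

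**What to change.** 1. In Secondary aims and in the Life-ON 3 design section, restrict the aim, and hence the conclusion, to prevention of postpartum depression.
2. Add a secondary outcome: first onset of minor or major depression from allocation to 12 months postpartum. It uses data already collected and makes prevention during treatment, or delay past birth, visible.
3. In Statistical analyses, replace the comparison of women who had light with untreated women by a comparison of all women by randomised arm (BLT versus no treatment). Women with onset before birth, or who enter Life-ON 2, stay in their allocated group.

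The cost is one extra secondary analysis and a narrower stated aim, with no added women or visits. The secondary outcome mixes antenatal and postpartum onsets, and with sparse antenatal checks it will miss episodes that remit between visits.

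If the sponsor wants to keep the claim about PND, onset from allocation can become the main outcome instead. The power loss in the table should then be accepted openly: 0.81 to 0.71–0.76 at 15 % vs 5 % if light has no effect before birth.

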### Safety assessment

The safety assessment will consist of monitoring and recording of Adverse Reactions (ADRs) and Serious Adverse Event (SAE) only for substudies involving treatment with BLT.

### Determination of sample size

This prospective, longitudinal cohort study will include 500 pregnant females. Given that we consecutively include participants, we judge this sample size as sufficient to generate estimates for the prevalence of perinatal depression, sleep disturbances, and sleep disorders during pregnancy and postpartum. Based on a meta-analysis of prevalence and incidence studies we expect the cumulative incidence of minor and major depression during late pregnancy and postpartum to be at least 20 % (*n* = 100). Taking into consideration that we plan to include 80 females in a trial of light treatment for the prevention of postpartum depression, we expect that approximately 300 females will be symptom free, while 100 to 150 females will experience minor or major depression during the perinatal period. For the study of risk factors involved into the development of perinatal depression, our sample size will enable the detection of small to moderate effects (d > 0.3) with an adequate statistical power (≥80 %).

For the Life-ON study no significance threshold a priori is considered.

The main outcomes of Life-ON 2 will be the change of depressive symptoms, response and remission rates after 6-week bright light treatment versus placebo. Based on a previous meta-analysis we expect that the prevalence of depression during the perinatal period will be at least 25 %, which would qualify 125 participants for inclusion in the treatment trial. From our previous experiences we anticipate an attrition rate of 25 % for reasons of refusal, non-compliance, or necessity for additional/alternative treatment. A conservative estimate would, therefore, be that 80 females will complete the treatment trial. At the same time, weekly monitoring is expected to increase compliance and reduce attrition and the available data suggests that prolongation of the treatment duration to 6 weeks will increase the bright light versus placebo difference. Our conservatively planned sample size (40 versus 40) will enable us to demonstrate medium effects (d >0.56) with a one-side error level of 0.05 and adequate statistical power (≥80 %).

Concerning the substudy Life-ON 3, previous meta-analyses have estimated an incidence of 15 to 49 % for the onset of minor and major depression during a 12 months’ postpartum period. Our sample size calculation is based on an assumed incidence of 20 % in females receiving no treatment and we expect this incidence to be reduced to 5 % in females receiving bright light treatment during late pregnancy. With a planned allocation ratio of 1:3 and a one-sided alpha level of 0.05, comparison of 43 treated females to 172 untreated subjects will yield an adequate statistical power (≥80 %). Assuming an even lower incidence of 15 % in untreated subjects, sample size calculations indicate that inclusion of 79 vs. 314 subjects will be needed to demonstrate a reduced incidence (5 %) with adequate statistical power. We therefore plan to block-randomise consecutive participants on a 1:3 basis to BTL versus no treatment until 80 participants have received active light treatment.

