### Description of the study

The Life-ON Project is a prospective, both observational and interventional, multicentre [three sleep centres in Northern Italy (Bologna, Milan, Turin) and one in Southern Switzerland (Lugano)], non-profit, without medicines, cohort study, which will include about 500 women, who will be longitudinally followed from early pregnancy (10–15 gestational week) until 12 months after delivery. Pregnant females attending the outpatient clinics of the involved centres and who gave voluntary written informed consent to participate in the study (Life-ON) will be included consecutively. Inclusion and exclusion criteria are listed in Table 2.

**Table 2 Tab2:** Inclusion and exclusion criteria

Inclusion criteria	Exclusion criteria
• Age 18–45 years • Free of any major medical condition • Normal ocular function • Gestational age between 10 to 15 weeks at time of screening • Written informed consent	• Diagnosis of bipolar I or II disorder (DSM-5) • Recent history (less than 6 months) or current major depression or an Edinburgh Postnatal Depression Scale (EPDS) score > 12 at time of inclusion • Any psychotic episode, substance abuse, recent history of suicide attempt (less than 12 months) • Use of antidepressants or other pharmacologic treatments for depression in the last 6 months • Intrauterine fetal death

Participating women will undergo scheduled clinical examinations by a multidisciplinary team including a gynaecologist and/or obstetrician, a psychologist or psychiatrist and a neurologist expert in sleep disorders. During the periodic follow-up visits, medical/gynaecological, psychological and sleep will be assessed by structured interviews and validated scales and questionnaires (Table 3).

**Table 3 Tab3:** Psychiatric and sleep assessment tools

Psychiatric assessment tools

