### Statistical analyses

Standard parametric or non-parametric statistical tests will be employed to explore differences between females with onset of depression to those remaining symptom free. To take full advantage of the longitudinal study design, generalized mixed modelling will be employed to test whether sleep-related and other fixed or variable markers can predict the onset of perinatal depression, possibly in a time-associated manner. The evaluation of BLT effectiveness for perinatal depression should take into account that this therapy will be applied at different times during the perinatal period; therefore, this will be included as a covariate in the ANCOVA (continuous data) and logistic regression analyses (dichotomous data, proportions). Regarding the efficacy of BLT in prevention of post-partum depression we will use logistic regression analysis to compare incidence rates between the group of not-depressed patients who received light therapy during pregnancy versus untreated subjects. For all analyses *p* values < 0.05 will be considered significant. The statistical analysis will be performed using a dedicated software (SPSS, IL, USA).

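### The cohort excludes women depressed at entry, so it can estimate the incidence of new onset after 10–15 weeks but not the prevalence of perinatal depression, and the 80 women given preventive light shift a crude rate

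*Protocol article*

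**What the plan says.** All references are to the protocol article.

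- **Determination of sample size.** "This prospective, longitudinal cohort study will include 500 pregnant females". Because inclusion is consecutive, that number is judged "sufficient to generate estimates for the prevalence of perinatal depression, sleep disturbances, and sleep disorders during pregnancy and postpartum". The next sentence expects a cumulative incidence of minor and major depression in late pregnancy and postpartum of at least 20 % (n = 100).
- **Background.** Perinatal depression (PND) is major depression with onset at any time in pregnancy or in the 12 months after delivery. Around half of cases are said to begin during pregnancy.
- **Description of the study, Table 2.** Entry is at 10–15 gestational weeks. Exclusions include "Recent history (less than 6 months) or current major depression or an Edinburgh Postnatal Depression Scale (EPDS) score > 12 at time of inclusion" and "Use of antidepressants or other pharmacologic treatments for depression in the last 6 months".
- **Life-ON 3 and its sample size.** Within the same cohort "we plan to include 80 females in a trial of light treatment for the prevention of postpartum depression". They are undepressed women treated in the third trimester, block-randomised 1:3 against no treatment. Incidence is expected to fall from 20 % to 5 %.
- **Statistical analyses.** The marker analysis is to "explore differences between females with onset of depression to those remaining symptom free".

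**The concern.** Consecutive recruitment supports a prevalence estimate only if the women recruited represent the population in question. Here the entry criteria select on the outcome. A woman whose depression began at week 6 has PND by the Background definition and cannot enter. What is left is a cohort at risk of new onset. That is the right population for predicting onset, but the wrong one for prevalence. If the result were reported as prevalence, it would be set beside figures such as the roughly 12 % in the Background, which concern a different quantity.

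The second matter concerns the rate itself. Sixteen per cent of the cohort (80/500) receives an intervention that the plan expects to prevent the event being counted. A rate over all 500 then mixes treated and untreated risk. A rate that leaves the 80 out removes only women who had reached the third trimester undepressed.

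**Working it through.** **1. The plan's own figures.** 0.20 × 500 = 100 cases, as stated. The groups given are 80 in the prevention trial, about 300 symptom free and 100 to 150 depressed. They sum to 480 and 530, which brackets 500. The count therefore suggests that the 80 are a separate group, without saying so.

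**2. Entry exclusion.** Let q be the share of consecutive women excluded because a PND onset fell between conception and entry. The article does not give q. Take 20 % as the incidence after entry and assume that the remaining women share it. Then:

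- whole-population figure = q + (1 − q) × 0.20
- gap to the cohort figure = 0.80 × q

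For assumed q of 1, 2 and 5 % the whole-population figure is 20.8, 21.6 and 24.0 %.

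**3. Yardstick.** The 95 % half-width at 20 % and n = 500 is 1.96 × √(0.20 × 0.80 / 500) = 3.5 points. The gap in step 2 passes this at q of about 3.5 / 0.80 = 4.4 %.

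**4. The 80 treated women.** Take 100 cases in 500 without BLT.

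- *No onset before BLT, so the full 20 % untreated risk applies to the 80.* Pooled rate = (420 × 0.20 + 80 × 0.05)/500 = 88/500 = 17.6 %, a shift of −2.4 points.
- *Half of onsets before BLT (assumption, taken from the Background's statement on antenatal onset).* 50 cases come first and 450 women remain, with a residual risk of 50/450 = 11.1 %.
  - BLT lowers risk to 5 %: 80 × (0.111 − 0.05) = 4.9 cases fewer, so 95.1/500 = 19.0 %, a shift of −1.0 point.
  - BLT has the plan's relative effect (1 − 5/20 = 75 %): 80 × 0.111 × 0.75 = 6.7 cases fewer, so 93.3/500 = 18.7 %, a shift of −1.3 points.
- *The 80 dropped, same half-antenatal assumption.* (100 − 80 × 0.111)/420 = 91.1/420 = 21.7 %, a shift of +1.7 points. With no onset before BLT this shift is nil: (100 − 16)/420 = 20.0 %.
- *The light arm censored at the start of BLT, same assumption.* 1 − (450/500) × (1 − 50/450) = 1 − 0.90 × 0.889 = 20.0 %. The untreated rate is recovered.

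Half before BLT is probably high, because onsets before entry are already excluded and some antenatal onsets come after BLT has started. The pooled shift then lies between −1.0 and −2.4 points.

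**5. Marker contrast.** This was simulated with 4 million draws. The marker was standard normal with log odds ratio 0.3 per SD, and 16 % were randomised to BLT, with 20 % risk untreated and 5 % treated. The standardised difference d between depressed and undepressed women was 0.298 in untreated women and 0.292 with all women pooled. If BLT prevented every case, pooled d was 0.288.

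**The case against.** **It is loose wording, and prevalence is not an aim.** The sentence after the claim turns to cumulative incidence, the analysis section speaks of onset, and neither the primary nor the secondary aims mention prevalence. This stands as a limit on the consequence. It does not remove the claim, which is offered as the ground on which 500 women are judged enough.

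**Most excluded women may not be missed PND cases.** At 10–15 weeks a six-month look-back reaches to before conception, and depression that began then is not PND by the Background definition. This stands. A reader might put the whole excluded share into the formula of step 2 and infer that true prevalence is 24–32 % (shares of 5–15 %). The document supports neither that share nor counting every exclusion as a case.

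**The article does not specify a pooled rate, and handling of the 80 may be set out in the full protocol.** This stands too. The silence is not a fault in itself, and the counts in step 1 suggest that the 80 are kept apart. The arithmetic shows only that neither simple choice gives the untreated incidence, so the restated estimand needs a rule.

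**A reader might infer that the primary risk-factor contrast is biased.** The document does not support this. Excluding women already depressed is proper when predicting onset. BLT is randomised, so it is independent of markers measured earlier. Polysomnography and the first actigraphy are at weeks 23–25, before third-trimester BLT. The change in d from 0.298 to 0.292 is negligible. Only markers measured after BLT, such as postpartum actigraphy and later sleep and mood scales, could be altered by it.

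**Conclusion.** The stated property does not hold: a cohort cleared of depression at 10–15 weeks cannot give the prevalence of PND as the article defines it. It can give the cumulative incidence of new onset from entry to 12 months postpartum among women who meet Table 2. The distance between the two is 0.80 × q at a 20 % incidence. Since q is unknown, no size can be claimed.

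For the incidence itself, pooling the 80 treated women lowers the rate by about 1.0–1.3 points on the half-antenatal assumption and by at most 2.4 points. Dropping them raises it by up to about 1.7 points on the same assumption. All of these lie within the 3.5-point half-width, and all assume that BLT works as the plan expects. The point changes what may be concluded from the descriptive estimate. The primary aim is not impaired.

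**What to change.** 1. In the sample-size section, replace prevalence of perinatal depression with the cumulative incidence of new-onset depression from 10–15 weeks to 12 months postpartum in women without recent depression at entry, as Table 2 defines it.
2. Estimate it with a time-to-onset method that censors the Life-ON 3 light arm at the start of BLT. Alternatively, weight the untreated randomised women to stand in for the light arm: at 1:3, each carries weight 4/3. Because Life-ON 3 needs separate consent, weighting is the safer choice if consenting women differ from the rest.
3. Include BLT arm as a covariate in the marker models, mainly for markers measured after BLT.

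No new data are needed. The cost is a narrower epidemiological claim and a little more analysis.
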